#### Quality of life

2.4.4

Enrolled participants are asked to complete paper questionnaires in person before the start of the treatment, before the 4^th^ treatment session at a dose of 12 Gy and at the first follow-up visit post-treatment. EORTC questionnaires have been designed, tested and validated to evaluate health-related quality of life in cancer patients and have been used widely used in clinical trials (32). To assess the individual quality of life during and after hyperthermia treatment, QoL questionnaires will be scored according to the guidelines of the quality of life group (36). The scores will be compared longitudinally to evaluate individual quality of life progression over time using a Mixed Model for Repeated Measures.

#### Recurrence-free survival, distant-metastasis-free survival and overall survival

2.4.5

For the analysis of recurrence-free survival, distant metastasis-free survival and overall survival, the dates of loco-regional recurrences and distant metastasis and the time of death are recorded during follow-up. The date of loco-regional recurrence is defined as the date of detection of metastasis in the ipsilateral breast, nearby lymph nodes or chest wall. Recurrence-free survival is defined as the survival between start of treatment and the date of detection of locoregional recurrence. Distant metastasis-free survival is defined as the time between onset of treatment until the date of detection of distant metastasis. Overall survival is defined as the time between start of treatment and death. Correlation of clinical and pathologic outcome with recurrence-free survival, distant metastasis-free survival and overall survival are analyzed using Kaplan-Meier-plots and log-rank tests. Cox regression will be used to model the dependence on three additional variables.

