Radiotherapy may be combined with mild locoregional hyperthermia (HT), i.e., the local heating of the tumor-bearing tissue to 39°C – 43°C (4, 15), administered before or after radiotherapy (16, 17). A non-invasive method for heating superficial malignant tissue is the application of the water-filtered infrared A (wIRA) irradiation to the treated tumor area (17). This method results in peak temperatures (~ 42°C) in the superficial layers of the skin. In 20 mm of tissue depth, wIRA can yield temperatures of approximately 40°C (17–19).

Mild hyperthermia causes radiation sensitization of tumor cells by (a) improving tissue oxygenation (20), (b) inhibiting DNA repair mechanisms and (c) stimulating the immune system without causing direct cytotoxic effects in normal tissue (15, 16). In addition, hyperthermia at temperatures >42°C for a longer exposure time leads to direct cytotoxicity of hypoxic and nutrient-deprived cells (21, 22). These effects on radiosensitivity have been demonstrated to be most prominent with a very short time interval between hyperthermia and irradiation (23). Therefore, we apply radiotherapy within <5 minutes after hyperthermia. This approach ensures the effective utilization of hyperthermia-associated tissue oxygenation. By employing this combination treatment strategy, local tumor control can be achieved with a significantly lower radiation dose than with radiotherapy alone, allowing effective and tolerable treatments even after multiple prior irradiations of the affected body region (16, 24–26). Hyperthermia combined with radiotherapy offers a treatment option for patients for whom neither surgery nor conventional fractionated radiotherapy is an appropriate or effective treatment option, and for patients with otherwise treatment-resistant tumors. The likelihood of achieving a complete remission with HT + re-irradiation is inversely correlated to tumor extent (16, 27). wIRA hyperthermia combined with a hypofractionated re-irradiation scheme of 5x 4 Gy/week, administered immediately after hyperthermia, has demonstrated very high success rates in breast cancer patients with recurrent disease (16, 19). At the same time, weekly treatment sessions may alleviate the treatment burden for patients (16, 19).

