### Patients

2.2

Patients with local or (loco)regional recurrent (LRR) breast cancer after mastectomy, who present at the Department of Radiation Oncology at the Medical Center – University of Freiburg, Germany or in the interdisciplinary breast cancer tumor boards, will be screened for participation in the study. Patients with locoregional disease as classified according to the r-classes I-IV defined by Notter et al. (16) are eligible for the study. Central inclusion criteria is the indication for local mild superficial hyperthermia applied by wIRA combined with low-dose re-irradiation, i.e., patients with inoperable LRR that have a maximum depth extension of 20 mm. In addition, patients must (1) provide written, informed consent prior to enrollment and (2) be >18 years of age. Age <18 years, intolerance to local anesthetics, pregnancy, and lack of capacity to consent are exclusion criteria for this study. Distant metastases do not represent an exclusion criterion since they are common in patients with unresectable, locoregional recurrent breast cancer. Written informed consent was approved by the local ethics committee and will be obtained by the principal investigator from patients after sufficient time to read the patients’ information and discuss any questions. Informed consent to use biomaterial and associated data is collected using the informed consent form of the Center for Biobanking, Medical Center – University of Freiburg. Expected recruitment rates are high (>90%).

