Treatment response is clinically evaluated and (photo-)documented weekly during the course of the treatment. At a dose of 12 Gy, a second punch biopsy is taken from the same tumor lesion for diagnosis of treatment response by evaluating tumor cell quantity and proliferation. Where applicable, another blood sample is taken. In case of a continuously high density of intact tumor cells and/or a high proliferation rate, a sixth treatment session may be considered to increase the total dose to 24 Gy. The success of the treatment is clinically evaluated at a follow-up appointment 6 weeks after completion of treatment. Another punch biopsy is taken to evaluate the histologic response and another blood sample will be drawn for further analysis. Clinical follow-up continues at 3-months intervals for one year, followed by 6 months intervals up to 5 years.

The total radiation dose administered may need to be adjusted on an individual basis. Patients who cannot continue treatment due to generalized progression or other reasons may receive a total dose of less than 20 Gy. When possible, these patients are monitored for treatment response and follow-up is performed as scheduled.

Furthermore, questionnaires are employed to assess patients’ individual quality of life before and during therapy and at the first follow-up appointment. This assessment is conducted using a standardized quality of life questionnaire sourced from the European Organization for Research and Treatment of Cancer (EORTC), EORTC QLQ-C30 (32), and an additional study-specific module on the tolerability of hyperthermia.

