#### Baseline data

2.4.1

At enrolment, baseline demographic data and relevant clinical data about the course of the disease and treatment to date are retrieved from medical records and documented. These include date of diagnosis, localization and pathology of the primary tumor and of recurrences/distant metastases, previous and current therapies, and current disease stage and symptoms.

Study data are collected and managed using the Research Electronic Data Capture (REDCap) tool hosted at the Medical Center - University of Freiburg, Germany (33, 34). REDCap is a secure, web-based software platform designed to support data capture for research studies, providing (1) an intuitive interface for validated data capture; (2) audit trails for tracking data manipulation and export procedures; (3) automated export procedures for data downloads to statistical packages; and (4) procedures for data integration and interoperability with external sources (33, 34). Study records are pseudonymized and access to identifying information of the participants is strictly limited. Data will be retained for 10 years in accordance with policy.

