#### Local clinical and histological tumor response

2.4.2

The primary outcome of the HISTOTHERM study is the evaluation of local clinical and histological tumor response. Clinical tumor response is evaluated guided by the assessments defined by RECIST; notably complete response (disappearance of target lesion), partial response (>30% decrease), stable disease (< 30% decrease, <20% increase) and progressive disease (>20% increase) of the treated tumor (35). Since imaging diagnostics (CT/MRT) is not indicated as a standard therapy control during course of the treatment, treatment response is evaluated according to the investigator’s assessment. Clinical evaluation includes optical control, photographic documentation and palpation and is done during treatment and at follow-up visits six weeks after end of treatment followed by three-months intervals for the initial year and six-months intervals thereafter, for a cumulative duration of five years. Local clinical response is reported as discrete data (36).

Pathological regression is evaluated on Hematoxylin-Eosin (H&E) stained slides with Cytokeratin stained sections as reference according to the grading system of Miller-Payne in pre- and post-treatment samples (37). Frequency distribution and descriptive statistics are employed for the characterization of the treatment response. In order to compare molecular profiles and survival of different treatment responses, patients are grouped according to their clinical and histologic response. We will employ a generalized linear mixed model with Poisson distribution for evaluation.

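### Overall survival is compared between response groups by log-rank with no stratum named, in a cohort that mixes patients with and without distant metastases; metastatic status at entry should be the stratum and a named Cox variable

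*Protocol article*

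**What the plan says.** - **Who enters (Protocol article, 2.2 Patients).** "Distant metastases do not represent an exclusion criterion since they are common in patients with unresectable, locoregional recurrent breast cancer". The mix is intended, and the text expects it to be frequent.
- **What is recorded at enrolment (2.4.1 Baseline data).** The list includes "localization and pathology of the primary tumor and of recurrences/distant metastases", so metastatic status at entry is available for every patient.
- **How groups are formed (2.4.2).** "In order to compare molecular profiles and survival of different treatment responses, patients are grouped according to their clinical and histologic response". These groups arise after entry and are not randomized.
- **What the endpoint is (2.4.5).** "Overall survival is defined as the time between start of treatment and death".
- **How survival is compared (2.4.5).** Clinical and pathologic outcome are set against three time-to-event endpoints, and the text says that "overall survival are analyzed using Kaplan-Meier-plots and log-rank tests". No stratification factor is mentioned.
- **What is adjusted for (2.4.5).** "Cox regression will be used to model the dependence on three additional variables". The number is fixed, but none of the three is named.

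**The concern.** A log-rank test between groups formed by response describes an association. A prognostic factor that differs between the groups can produce that association by itself. Distant metastatic disease at entry is an obvious candidate because it bears on death whatever happens on the chest wall. If patients with metastases also respond less often locally, the non-responder group will contain more of them. It will then die earlier even if local response does nothing for survival.

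What is at stake is interpretation. A separation of the curves could be taken to show that local control prolongs life, when it reflects who already had distant disease. The article hopes to find markers that may guide later treatment decisions, so a misread link between response and survival would carry forward.

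**Working it through.** **The plan's own figures.** No significance level, event count or survival effect is stated. The only figures in 2.5 that can be recomputed are workload counts: (3 biopsies + 1 earlier tissue sample) × 20 antibodies = 80 sections per patient, and 80 × 40 = 3200. Both reproduce, and neither bears on this point.

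**Inputs from the article.** 40 patients (2.5), follow-up up to 5 years (2.3), and survival counted from start of treatment (2.4.5).

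**Assumed inputs, because the article gives none.**
- Metastatic share at entry: 30% or 50%, that is 0.30 × 40 = 12 or 0.50 × 40 = 20 patients.
- Median survival without metastases: 48 months, exponential, so the monthly hazard is ln 2 / 48 = 0.0144.
- Death hazard ratio, metastatic v non-metastatic: 2, 3 or 4 (medians 48/2 = 24, 48/3 = 16, 48/4 = 12 months).
- Response rates as in the table; staggered censoring, at most 60 months.
- Response has **no** effect on survival. Test two-sided at 5%.

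**Statistic.** At each death, let p be the share of responders among those at risk and G = 1 if the patient who died was a responder. Then U = Σ(G − p), V = Σp(1 − p), and the test rejects if U²/V > 3.84. The one-step hazard ratio is exp(U/V). The stratified version forms U and V within each metastatic stratum and adds them.

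**Results, 4000 simulated studies per scenario** (ranges run over both shares and all three hazard ratios):

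| Response, non-metastatic / metastatic | Rejections, no stratum | Apparent hazard ratio, no stratum | Rejections, stratified |
|---|---|---|---|
| 60% / 60% | 4.6% to 5.7% | 0.99 to 1.01 | 4.8% to 5.7% |
| 70% / 50% | 7.0% to 12.5% | 0.88 to 0.76 | 5.2% to 6.2% |
| 70% / 40% | 7.8% to 16.6% | 0.82 to 0.67 | 4.4% to 6.1% |
| 80% / 40% | 11.4% to 27.3% | 0.75 to 0.57 | 5.4% to 5.8% |

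Nearly all the excess rejections favor responders. The stratified hazard ratio stays between 0.98 and 1.02. The scenarios yield about 21 to 27 deaths.

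**Second set of assumptions** (half metastatic, medians 48 v 18 months unless stated, follow-up 12 to 60 months), without v with stratification:
- 70/50% response: 8.5% v 5.2%
- 80/50%: 12.6% v 5.2%
- 80/40%: 16.6% v 5.9%
- 80/40% with medians 48 v 12 months: 26.9% v 6.0%

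**Where the effect fades.** With equal response rates the test without a stratum keeps its level (5.6%). With a 10-point gap and 30% metastatic it rejects in only 6.0%.

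**Power.** With equal response rates and an assumed true hazard ratio of 0.4, power is 41% without and 44% with stratification, so two strata cost nothing there.

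**The case against.** The strongest reply is that this reads too much into a condensed article. Four parts of it deserve an answer.

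1. **Silence is not a commitment to an unstratified test.** Correct. The article neither names nor excludes a stratum, and a full protocol or analysis plan may supply one. A reader might infer that a plain log-rank test is fixed; the text does not go that far. What stands is that the section does specify the test and the number of covariates, yet does not tie either to the feature that 2.2 builds into the cohort.
2. **Adjustment is already planned.** An unadjusted display followed by a Cox model is conventional, and metastatic status could be among the three variables. That is so, but nothing assures it, and the log-rank result would be reported uncorrected in any case.
3. **No link between metastases and local response is stated.** This also stands. It is tempting to read one into 2.3: "Patients who cannot continue treatment due to generalized progression or other reasons may receive a total dose of less than 20 Gy". That sentence concerns progression during treatment, not status at entry, and reports no response rates. The Introduction says "The likelihood of achieving a complete remission with HT + re-irradiation is inversely correlated to tumor extent", which is about tumor extent and does not mention metastatic status. The link is plausible, no more.
4. **The analysis is exploratory.** Survival is not the primary outcome, 40 patients were chosen on pragmatic grounds, and the article speaks of correlation. The consequence is a possibly misleading association, not a failed test of a stated hypothesis.

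**Conclusion.** The point holds in a conditional form. The cohort mixes patients with and without distant metastases by design, overall survival is compared between non-randomized response groups with no stratum named, and the three Cox variables are unnamed. If local response differs by metastatic status at entry, the comparison can show a spurious benefit.

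For response gaps of 20 to 40 percentage points and a metastatic share of 30% to 50%, false positives are about 7% to 27% without stratification and about 4% to 6% with it. The upper end needs both the widest response gap and the widest survival gap. With no response gap there is no inflation. The shares, response rates and survival times are all assumptions.

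A reader might infer that the definition of overall survival is faulty or that the study's conclusions are invalid. Neither follows: the definition is ordinary, and this is a worthwhile improvement to a non-primary, exploratory analysis. It is also separate from the fact that response becomes known only after the survival clock has started, which stratification would not cure.

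**What to change.** In 2.4.5, amend the log-rank and Cox sentences:

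- Stratify the log-rank test of overall survival by distant metastases at entry (yes/no).
- For this test, collapse response to few groups, for example responder v non-responder. Four clinical categories in two strata make 4 × 2 = 8 cells, on average 40 / 8 = 5 patients each.
- Name distant metastases at entry as one of the three Cox variables.
- Optionally, show the Kaplan-Meier curves split by that status.

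Settle this before survival is analyzed by response, so that the covariate choice does not depend on the results.

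**Cost.** Wording only: 2.4.1 already collects the variable, and no visit, sample or patient is added. Some precision may be lost with 40 patients in two strata, particularly if response and metastatic status are closely related. Collapsing response gives up detail between grades.

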### Interventions

2.3

Patients enrolled in the HISTOTHERM study are treated according to the standard operating procedure for the combination treatment of hyperthermia and radiotherapy at the study center. The area to be treated is irradiated with 20 Gy in single doses of 4 Gy every 7 days, immediately (i.e., within 2-5 min) after application of local hyperthermia, for 5 consecutive weeks in general. Radiation treatment planning is conducted based on computer tomography (CT) scans, with 8-10 mm expansion of clinical target volume (CTV) to obtain planning target volume (PTV). The choice between electron fields or volumetric modulated arc therapy (VMAT) plans is determined by the patients’ anatomy. To ensure precise positioning for VMAT plans, cone beam CT is used for correct patient alignment. Furthermore, surface optical scanning is employed to monitor and verify patient positioning accuracy. No RT-boost is applied. Re-planning is done if clinically indicated. Superficial hyperthermia is applied with thermography-controlled wIRA using the TWH 1500 wIRA-hyperthermia system (Hydrosun^®^, Müllheim, Germany) in order to locally heat the tissue volume to be irradiated to a temperature of 39°C-43°C for 60 minutes. Superficial tissue temperatures are thermography-monitored and automatically recorded as a treatment protocol. This documentation contains both temperature curves and thermographic images for each minute of treatment. Prior to the first treatment session, a punch biopsy is taken to confirm the initial diagnosis and to re-assess the histologic profile of the tumor. The biopsy is performed under local anesthesia using a 2.0 mm-3.0 mm disposable biopsy punch. The size of the punches is selected to obtain sufficient material without suturing the wound. Blood is collected from eligible patients using aseptic techniques in EDTA blood collection tubes (9 mL).

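### Survival counted from start of treatment is compared between response groups formed only later, so the comparison can favour responders; a landmark at the 6-week visit avoids this

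*Protocol article*

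**What the plan says.** All three time-to-event endpoints in section 2.4.5 share one origin:

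- "Overall survival is defined as the time between start of treatment and death"
- "Recurrence-free survival is defined as the survival between start of treatment and the date of detection of locoregional recurrence"
- The metastasis endpoint likewise has its clock set at treatment onset.

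The groups to be compared come from section 2.4.2: "In order to compare molecular profiles and survival of different treatment responses, patients are grouped according to their clinical and histologic response". Section 2.4.5 gives the method: "Correlation of clinical and pathologic outcome with recurrence-free survival, distant metastasis-free survival and overall survival are analyzed using Kaplan-Meier-plots and log-rank tests". It adds: "Cox regression will be used to model the dependence on three additional variables". Those variables are not named, and response is not described as time-dependent.

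On timing, section 2.3 states: "The area to be treated is irradiated with 20 Gy in single doses of 4 Gy every 7 days", for five weeks as a rule, with a possible sixth session. It continues: "The success of the treatment is clinically evaluated at a follow-up appointment 6 weeks after completion of treatment". The biopsy for histologic response is described with that visit, and Miller-Payne grading (section 2.4.2) needs a post-treatment sample. Clinical response is also judged weekly during treatment and at follow-up visits for up to 5 years.

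The article does not say which assessment defines the groups, or where a patient belongs who dies or drops out before it. It mentions no landmark and no later time origin for this comparison.

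**The concern.** The grouping variable does not exist at the time origin. To be labelled a responder at the 6-week visit, a patient must live to that visit. The weeks before it are therefore event-free by construction for responders, and any early deaths can fall only on the other side or outside the comparison. If they fall among the non-responders, responders appear to live longer even when response has no bearing on survival. A rule that lets response be first recorded at later visits lengthens the guaranteed period.

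Early failures are foreseen. Section 2.2 admits patients with distant metastases, and section 2.3 provides for patients who stop early because of generalized progression.

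Recurrence-free survival has a further overlap. Progressive disease of the treated tumor is a response category (section 2.4.2), and the recurrence event is disease found in the ipsilateral breast, nearby nodes or chest wall (section 2.4.5). Local progression seen at the response visit can then be both the group label and the event.

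At stake is whether a reported link between response and survival reflects biology or the way the groups were formed. The study wants to find markers of response that could later guide treatment, so a spurious link would make response look like a better stand-in for survival than it is.

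**Working it through.** **Plan's own figure.** The article gives no number for this comparison. The 40 patients of section 2.5 are set on pragmatic grounds, with no error rate, power or event count to reproduce.

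**Step 1: when response is known.** Inputs from section 2.3: sessions every 7 days, five or six sessions, visit 6 weeks after the last.

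Visit day = (sessions − 1) × 7 + 42

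- Five sessions: 4 × 7 + 42 = day 70, week 10.
- Six sessions: 5 × 7 + 42 = day 77, week 11.

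**Step 2: share of patients dying before week 10.** Median survival is not in the article, so a range is assumed. With exponential survival and 4.348 weeks per month, the share is 1 − 2^(−10 / (4.348 × median in months)).

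| Assumed median (months) | Share dead by week 10 | Expected of 40 |
|---|---|---|
| 6 | 23.3% | 9.3 |
| 12 | 12.4% | 5.0 |
| 24 | 6.4% | 2.6 |
| 36 | 4.3% | 1.7 |

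**Step 3: effect on the log-rank test when response has no effect.** Null simulation of a single survival endpoint: 40 patients, two-sided 5% test, 4,000 runs per cell, response drawn independently of survival, censoring uniform over 1 to 5 years. Response rates of 50% and 70% are assumptions. Response is fixed at week 10, early deaths count as non-responders, and the clock starts at treatment. HR is the median apparent hazard ratio for responders; the truth is 1.0.

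| Median (months) | False positives, 50% responders | HR | False positives, 70% responders | HR |
|---|---|---|---|---|
| 6 | 26.7% | 0.65 | 53.6% | 0.52 |
| 12 | 13.1% | 0.75 | 28.2% | 0.64 |
| 24 | 7.6% | 0.82 | 15.9% | 0.72 |
| 36 | 6.8% | 0.84 | 11.2% | 0.76 |

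Almost all of these false positives favour responders.

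**Step 4: response also first recorded later in year 1.** With an assumed 60/20/10/10% split over the week-10 visit and the next three quarterly visits, the false-positive rate over the same medians is 10.6-39.9% at 50% responders and 20.8-69.6% at 70%.

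**Step 5: landmark at week 10.** Keeping only patients alive at week 10, grouped by status then, gives false-positive rates of 4.5-6.4% and hazard ratios of 0.98-1.01 over all eight scenarios.

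**Step 6: unassessed patients dropped, clock left at treatment start.** The log-rank test uses only the order of event times. If nobody in either group can have an event before week 10, moving the origin by 10 weeks changes nothing in the test. A simulation with 60% responders gave 5.8%, 5.9%, 5.2% and 5.6% at medians of 9, 12, 24 and 36 months. Both Kaplan-Meier curves, however, stay at 100% for the first 10 weeks by construction.

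**The case against.** The strongest reply is that the distortion of the test needs a rule the article does not contain. Nothing says that a patient who dies before assessment is a non-responder. Such a patient may be not evaluable, and for Miller-Payne grading that is the natural reading, since there is no grade without a post-treatment sample. Step 6 shows that the test is then about nominal. This stands. A reader might infer from the mismatch alone that the log-rank test is necessarily biased; the article does not support that. What survives is that both curves would still be too favourable from treatment start and would describe only patients who reached the assessment.

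Second, clinical response is also judged weekly, so it could be fixed earlier. With response fixed at the last of five sessions (day 28), 60% responders and early deaths counted as non-responders, the false-positive rate is 10%, 8%, 6.7% and 6.4% at medians of 9, 12, 24 and 36 months. The problem shrinks but does not vanish, because the grouping still follows the time origin.

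Third, the handling of unevaluable patients is commonly left to a full protocol or analysis plan. That is fair, and its absence here is not the point. The point rests on what the article does fix: the time origin, the grouping variable and the test.

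Fourth, this is a secondary analysis in a 40-patient exploratory, non-interventional study; the primary outcome, local response, is untouched. This bears on severity, not on whether the comparison is sound.

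**Conclusion.** The point holds in conditional form and should be fixed; it is not critical to the study. The stated time origin and grouping variable do not fit together. If early failures count as non-responders, or if later visits can define response, the comparison is biased in favour of responders. With response fixed at week 10 the null false-positive rate is then roughly 7-54%, and 7-16% at medians of 24-36 months, against about 5% with a landmark. These figures rest on assumed median survival (6-36 months), response rate (50-70%), exponential survival and the censoring pattern; none of these is in the article. If unassessed patients are dropped at one fixed visit, the test is about nominal, but the curves from treatment start are too favourable. The overlap of group label and event in recurrence-free survival can arise under either rule.

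Two wider readings are tempting but not supported:

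- A reader might extend the fault to the Cox-type marker analyses. Section 2.4.3 does not say which sample enters them or when their clock starts, and a patient without a sample has no marker value rather than an unfavourable one.
- A reader might take this for the plan's only analysis linking response to outcome. Section 2.4.2 also names a Poisson mixed model in connection with the response groups.

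**What to change.** In section 2.4.5 or the analysis plan:

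1. Compare survival by response from a landmark at the 6-week post-treatment visit. Fix each patient's response group at that visit and start the clock there.
2. Include only patients alive at the landmark and, for the recurrence and metastasis endpoints, free of the respective event. This also keeps local progression at the visit from serving as both label and event.
3. If responses recorded later are to count, enter response as a time-dependent covariate in a Cox model instead.
4. State how patients without an assessment at the visit are handled, and report their number.
5. Keep start of treatment as time origin for whole-cohort curves.

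The cost is analysis wording only, with no new patients, visits or samples. The few patients with events before the landmark leave the group comparison but remain in the whole-cohort curves. Where local progression at the visit counts as a recurrence, those patients also leave the recurrence-free comparison, and the result applies only to patients who reached the visit event-free.
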